## Abstract

**Background:**

To date, research has found variable success in using attentional bias modification training (ABMT) procedures in pain samples. Several factors could contribute to these mixed findings, including boredom and low motivation. Indeed, training paradigms are repetitive, which can lead to disengagement and high dropout rates. A potential approach to overcoming some of these barriers is to attempt to increase motivation and engagement through gamification (ie, the use of game elements) of this procedure. To date, research has yet to explore the gamified format of ABMT for chronic pain and its potential for the transfer of benefits.

**Objective:**

The aim of this study is to investigate the effects of a gamified web-delivered ABMT intervention in a sample of adults with chronic pain via a randomized, double-blind, placebo-controlled trial.

**Methods:**

A total of 120 adults with chronic musculoskeletal pain, recruited from clinical (hospital outpatient waiting list) and nonclinical (wider community) settings, will be included in this randomized, double-blind, placebo-controlled, 3-arm trial. Participants will be randomly assigned to complete 6 web-based sessions of dot-probe nongamified sham control ABMT, nongamified standard ABMT, or gamified ABMT across a period of 3 weeks. Active ABMT conditions will aim to train attention away from pain-relevant words. Participant outcomes will be assessed at pretraining, during training, immediately after training, and at the 1-month follow-up. Primary outcomes include pain intensity, pain interference, and behavioral and self-reported engagement. Secondary outcomes include attentional bias for pain, anxiety, depression, interpretation bias for pain, and perceived improvement.

**Results:**

The ethical aspects of this research project have been approved by the human research ethics committees of the Royal Brisbane and Women’s Hospital (HREC/2020/QRBW/61743) and Queensland University of Technology (2000000395). Study recruitment commenced in August 2021 and is ongoing. Data collection and analysis are expected to be concluded by October 2022 and January 2023, respectively.

**Conclusions:**

This trial will be the first to evaluate the effects of gamification techniques in a pain ABMT intervention. The findings will provide important information on the potential therapeutic benefits of gamified pain ABMT programs, shed light on the motivational influences of certain game elements in the context of pain, and advance our understanding of chronic pain.

**Trial Registration:**

Australian New Zealand Clinical Trials Registry ACTRN12620000803998; https://anzctr.org.au/ACTRN12620000803998.aspx

**International Registered Report Identifier (IRRID):**

PRR1-10.2196/32359

## Introduction

### Background

Attention in individuals with chronic pain is often biased toward pain-related information (ie, word or picture stimuli) [1-3]. Such findings have led researchers to investigate whether these attentional biases can be modified with an attentional bias modification training (ABMT) procedure and whether this modification leads to changes in pain intensity and associated pain-related health outcomes [4]. ABMT protocols typically use a modified dot-probe task [5] to train participants to disengage from pain-related information and redirect attention to the competing neutral cues. To date, research has found variable success in using ABMT in pain samples (see the study by [name] et al [6] for an overview). Specifically, in the context of chronic pain, some studies have indicated that ABMT can be effective in improving pain-related outcomes (eg, pain intensity and pain-related disability) [4,7,8], whereas others have failed to replicate these positive effects [9,10].

Several factors could contribute to these mixed findings, including boredom and low motivation. Qualitative studies have indicated that participants experience dot-probe tasks as monotonous, repetitive, and boring [11,12]. Indeed, ABMT procedures require systematic repetition of numerous trials over multiple sessions across several weeks [4,7-10] and typically include a basic layout (ie, stimuli are presented on a plain background), which may make training sessions unappealing. The monotonous nature of such tasks could lead to (temporal) disengagement, low motivation, and high dropout rates, which in turn may compromise intervention efficacy. A potential approach to overcoming some of these barriers is to attempt to increase engagement through the gamification of ABMT. *Gamification* refers to the use of digital game elements (eg, points and avatars) in nonentertainment settings [13]. Qualitative [14] and quantitative [15] reviews on gamified cognitive training tasks have found that adding game elements to repetitive tasks improves motivation and engagement. However, Zhang et al [16], in their systematic review that focused specifically on gamified cognitive bias modification interventions for psychiatric disorders (ie, anxiety, affective, and addictive disorders), found that only 2 of the 4 identified studies reported gamified interventions to be effective [17,18], and only 1 study compared a gamified task directly against a nongamified counterpart [19]. This calls for more rigorously designed and theory-driven research in this field.

To date, research has yet to explore the gamified format of ABMT for chronic pain and its potential for the transfer of benefits. To address this gap in the literature, a gamified web-delivered pain ABMT intervention, based on the standard, modified dot-probe task [5], has been developed and augmented with game elements.

### Aims and Hypotheses

The aim of this study is to investigate the effects of a gamified web-delivered ABMT intervention in a sample of adults with chronic musculoskeletal pain via a randomized, double-blind, placebo-controlled trial. To do this, 3 ABMT conditions will be directly compared: nongamified sham control ABMT, nongamified standard ABMT, and gamified ABMT. It is hypothesized that the gamified ABMT condition, relative to both the standard ABMT and control ABMT conditions, will rate more highly on self-reported engagement (ie, task-related engagement, enjoyment, and interest) as well as complete more training sessions and have less dropout. On the basis of the findings from the broader ABMT literature and theoretical considerations [20-22], it is expected that the standard ABMT and gamified ABMT conditions will show a reduction in pain-related attentional biases and interpretation biases after training sessions, with the largest reduction in the gamified ABMT condition. Furthermore, it is expected that both the standard ABMT and gamified ABMT conditions, relative to the control ABMT condition, will show reductions in pain intensity, pain interference, anxiety, and depression scores immediately after training and 1-month later and that these reductions will be greater in the gamified ABMT condition compared with the standard ABMT condition. Finally, it is expected that both the standard ABMT and gamified ABMT conditions, relative to the control ABMT condition, will report global pain-related improvements following training and that these improvements will be larger in the gamified ABMT condition compared with the standard ABMT condition.

## Methods

### Study Design

This study is a randomized, double-blind, placebo-controlled, 3-arm, parallel-group trial examining the efficacy of a gamified ABMT for chronic pain delivered over the internet. Adults with chronic musculoskeletal pain will be randomly allocated to 1 of the 3 training conditions: control ABMT, standard ABMT, or gamified ABMT. The control ABMT condition comprises a dot-probe paradigm without training direction, whereas the standard ABMT and gamified ABMT conditions will aim to train attention away from pain-relevant words. Outcome assessments for all training conditions will be conducted via the internet at baseline, during training, immediately after training, and at the 1-month follow-up. Figure 1 shows the trial flow diagram. This study protocol is written in compliance with the SPIRIT (Standard Protocol Items: Recommendations for Interventional Trials) [23] guidelines.

**Figure 1 figure1:**
[figure not shown]
Flow diagram of study protocol. ABMT: attentional bias modification training.

### Study Setting

This trial will take place on the web; that is, all outcome assessments and training sessions will be conducted on the web at the participants’ place of convenience, using their own computers. The study focuses on adults with self-reported chronic musculoskeletal pain, recruited from both clinical (ie, outpatient waiting list) and nonclinical (ie, wider community) settings in Australia.

### Participants

To participate in this study, individuals must be aged ≥18 years; experience chronic musculoskeletal pain, that is, pain in bones, joints, muscles, or related soft tissues (eg, rheumatoid arthritis pain, nonspecific back pain, or fibromyalgia pain); meet the criteria for chronic pain, that is, self-reported pain that lasts or recurs for >3 months [24]; and have normal or corrected to normal vision. Participants will be excluded if they are not native English speakers or not fluent in reading and writing English (as participants’ reaction time [RT] to English words is used as an index of attentional bias to semantically related pain memory networks), have no access to a desktop or laptop computer connected to reliable internet (as the assessments and training sessions are conducted on the web), or are not able or willing to provide informed consent to participate.

### Recruitment and Consent

To optimize the generalizability of the findings, prospective participants will be recruited from a large Australian public hospital outpatient waitlist for pain management (clinical setting) as well as from a wider community (nonclinical setting). Individuals on the hospital outpatient waiting list who have been identified for screening using medical records will be invited to participate through personalized mail correspondence. These individuals may also be approached for recruitment at the introduction to persistent pain management orientation and information sessions held at the hospital every few months. Participants from the wider community will be recruited through university electronic mailing lists, distribution of flyers, social media, and community channels (eg, Facebook advertising, Twitter, LinkedIn, word of mouth, medical practices, and physiotherapy clinics).

All recruitment materials (eg, hospital personalized letters and flyers) will include a survey hyperlink that will direct prospective participants to the necessary study information to decide on participation. This will include information about the research procedures; the voluntary nature of the study, with the freedom to withdraw at any time until the collected data are deidentified (ie, upon completion of the 1-month follow-up survey); the potential risks and benefits of their participation; and whom to contact for questions about the research. All interested participants will be asked to provide informed consent electronically (ie, e-consent) before being taken to the screening questions and then to the first screen of the baseline assessment.

### Patient and Public Involvement

Public members with and without chronic pain have been involved in a prior validation study of pain-related and neutral visual word stimuli sets that will be used in this study ([name], [name], [name], [name], [name], unpublished data, April 2020). For this study, only patients and members of the public who meet the selection criterion of chronic pain experience will be eligible to participate.

### Randomization, Allocation Concealment, and Blinding

Participants fulfilling eligibility criteria and willing to participate in this study will be randomly allocated to 1 of the 3 training conditions after the baseline assessment. Randomization will be performed before participants are enrolled by an independent person blinded to all processes within the intervention, using a computerized random number generator. A block randomization technique will be used, allowing 6 participants at a time to be randomized in equal proportions to the 3 training arms. The allocation numbers will be stored on a password-protected university database maintained by the same independent person and will be revealed after participants are enrolled and baseline assessments are completed.

Each time a participant completes the baseline survey, an automatic email will be sent to the principal researcher ([name]). After receiving this email, the participant will be allocated to the next number on the list and, consequently, be assigned to a training arm. Researchers and participants will be blinded to group allocation throughout the trial (ie, double-blind study design). Furthermore, as assessments and training will occur on the web, in the absence of the investigators, the outcome data will be blinded. However, it is possible that a researcher could become aware of the participants’ training conditions to support them adequately in the instance of technical problems. However, it is unlikely that this will entail problems of bias allocation or assessment because of the web-based nature of the study.

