### Procedure

After informed consent is obtained and participants are eligible, they will complete the web-based baseline assessment (approximately 35 minutes) containing demographic questions as well as questions relating to their general health, current mental health, pain experience, and everyday thoughts and behaviors. At the end of the survey, participants will select their preferred days for training, which will be either (1) Monday and Thursday or (2) Tuesday and Friday. Participants will also be asked to provide an email address so that the research team can send links to the training sessions. Participants will then be randomized into 1 of the 3 groups and be invited by email to start their first training session. This email will include a weblink to the appropriate version of the intervention, as well as instructions on how to download the program.

Training sessions will be performed on the web at the participants’ time and place of convenience (using their own computers), twice a week on a separate pair of days (Monday and Thursday or Tuesday and Friday) for 3 consecutive weeks, totaling 6 sessions. This dosage is based on previous pain ABMT literature, which has shown positive training effects for dosages ranging between 4 and 8 sessions [4,7,8]. It is anticipated that the first and final sessions will take approximately 30 minutes, as it includes cognitive assessment measures, whereas sessions 2 to 5 will take approximately 15 minutes to complete. Participants will be asked to complete the sessions during normal waking hours and within 24 hours of receiving a web link. Each session will start with the same instructions, similar to those of previous research [10], and highlight the need to create a quiet and private environment free from distractions for at least 30 minutes. In total, the participants will be sent 6 session links. Necessary reminders will be sent via email and SMS text messages throughout the study.

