### Study Program

#### Overview

Participants will be involved in the trial for approximately 2 months, including a 3-week intervention period in which they will be randomized to 1 of the 3 training arms, followed by a 1-month follow-up period. Several strategies will be used to maximize participant retention and follow-up completion. First, we will adopt a web-based completion mode for the surveys and training sessions. Second, participants will receive a personalized email invitation for each training session. These emails will also provide participants the opportunity to ask the research team about any technical difficulties or other obstacles encountered while using the software. Third, we will use a combination of SMS text message and email message reminders according to the participants’ preferences. These reminders will be sent to the participants who do not complete the scheduled session within 24 hours of receiving the weblink. When there is no reaction to the training sessions and reminders after 2 weeks (ie, after 4 training sessions and 4 reminders), the participant will be considered as a dropout. Similarly, participants who fail to complete the follow-up assessments will receive up to 2 emails or SMS text message reminders: one after 24 hours and another one after 48 hours. Finally, the gamified ABMT intervention was developed using gamification features to encourage participants to keep using the program. No incentives will be provided to the participants.

Participant care (eg, rehabilitation program, exercise, cognitive behavioral therapy, and pain medications) concomitant with the ABMT (ie, control ABMT, standard ABMT, or gamified ABMT) will be permitted during the trial. It will be monitored through a *pain-treatment* question that will probe participants’ pain treatments and frequency since the commencement of the study or previous assessment.

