### Data Management and Monitoring

Owing to the minimal risks associated with study participation, it is not necessary to implement an independent data and safety monitoring board. The research team will be responsible for monitoring and data management and will meet regularly to manage the protocol, monitor recruitment, and deal with any adverse events. The reporting of this study will be conducted according to the CONSORT (Consolidated Standards of Reporting Trials) statement guidelines [79].

All data will be collected via the web using Qualtrics (Provo) for survey responses and Inquisit 6.4 for task data and self-reported engagement responses, and temporarily stored on these servers. Data safety and security measures have been considered, including restricted access to the research team, password protection, firewall, and virus protection. Furthermore, each participant will be assigned a unique participant code (blinded to the group the participant has been assigned to) and will be asked to self-generate an ID code (instead of participants’ personal information). Thus, this coded data may be reidentifiable during the research but will be deidentified upon completion of the study. An electronic, password-locked master file will be created that matches the unique participant code to their self-generated code to ensure participants are allocated to the correct experimental group and that the survey and task data match across the different time points. All data will be stored on a secure password-protected university server and accessed only by the research team. Upon completion of the project, electronic research data will be deposited in the university’s research data storage system and retained for a minimum of 15 years. The final coding scheme for outcome measures will be available from the authors upon request.

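### Researchers are said to be blinded throughout, yet the research team is described as routinely sending arm-specific session links; the primary behavioral engagement outcomes are the ones exposed

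*Protocol article*

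**What the plan says.** Under Randomization, Allocation Concealment, and Blinding, the protocol article states that "Researchers and participants will be blinded to group allocation throughout the trial" and labels the design double-blind. It then concedes that a researcher might learn a participant's condition while helping with a technical problem, and judges bias unlikely because the study runs on the web.

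The same section describes the allocation step: "Each time a participant completes the baseline survey, an automatic email will be sent to the principal researcher". After that email, "the participant will be allocated to the next number on the list and, consequently, be assigned to a training arm". An independent person generates the sequence and keeps the allocation database. That person is described as blinded to the processes of the intervention.

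The Procedure section says participants give an email address so that the research team can send them the session links. Of the invitation to the first session it says: "This email will include a weblink to the appropriate version of the intervention". Six session links are sent in all.

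The Overview under Study Program lists personalized invitations and reminders among the measures to maximize retention. On the invitations it adds: "These emails will also provide participants the opportunity to ask the research team about any technical difficulties".

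The primary outcomes in Table 1 include behavioral engagement, measured by intervention attrition and completion rates. The stated hypothesis is that the gamified arm will complete more sessions and have less dropout than the other two arms.

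**The concern.** A person who sends the correct version of a program to a participant ordinarily has to know which version is correct. If the team does this for every participant, researcher blinding is not lost only in occasional support cases. It is absent, for at least some of the team, from the first invitation.

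The stake depends on the outcome. Pain, mood and interest ratings are entered by participants alone at a computer, so staff knowledge has little way in. Attrition and sessions completed are different, because invitations and help with technical obstacles exist to keep people in the program. Staff who know the arm could, without intending to, help one arm more readily than another, and that would act directly on a primary outcome. Engagement is also where the trial expects its new finding, and the gamified task was designed by the authors themselves. A report that calls the trial double-blind without qualification would overstate the protection behind that result.

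**Working it through.** The point is one of consistency, and the plan gives no figure to reproduce. The check sets the statements side by side.

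1. **Property claimed.** Researchers are blinded throughout, with one exception for technical support (Randomization, Allocation Concealment, and Blinding).
2. **Trigger.** The notice that a participant is ready for allocation goes to the principal researcher, not to the independent person (same section).
3. **Allocation.** The next number on the list gives the arm, and the numbers are revealed after baseline. Both statements are in the passive voice, so neither the person allocating nor the recipient of the information is named.
4. **Link release.** The research team is named as the sender of session links, and the first invitation leads to the version for the participant's arm (Procedure). This is the firmest step, because it has a named actor and an arm-specific object.
5. **Does the exception cover step 4?** No. Technical support is occasional and depends on a problem arising. Link-sending happens for every participant, with six links planned for each.
6. **Is there a masking device?** None is described: no automatic redirect, no neutral link that resolves to the arm on a server, and no unblinded coordinator kept apart from the team. The independent person is given the sequence and the database, but is not said to send links.
7. **Does web delivery remove the consequence?** This depends on the outcome:
   - Self-completed questionnaires: largely yes.
   - Attrition and sessions completed: no. The same team issues invitations and answers technical queries (Study Program, Overview).
8. **How much discretion is there?** Limited.
   - Session reminders go to anyone who has not completed within 24 hours.
   - Follow-up reminders are capped at two, at 24 and 48 hours.
   - Dropout is defined by no response after four sessions and four reminders.
   - Completion is counted as sessions out of six, and a noncompleter is anyone who does not finish all six.
   - What remains open is mainly the technical help and the individual content of the invitations.

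**Conditional illustration only.** Suppose unequal contact shifted mean sessions completed by δ between two arms of 40, with no true effect and common SD σ. The two-sample t statistic then has noncentrality δ / (σ·√(2/40)). The documents give neither δ nor σ, so both are assumptions.

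| δ (sessions) | σ | Noncentrality | Chance of P<.05 |
|---|---|---|---|
| 0.25 | 2.0 | 0.56 | 8.6% |
| 0.25 | 1.5 | 0.75 | 11.4% |
| 0.50 | 2.0 | 1.12 | 19.7% |
| 0.50 | 1.5 | 1.49 | 31.3% |

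These values show what a shift of that size would do. They are no evidence that one would occur.

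**The case against.** The strongest reply is that the article never says the principal researcher learns the arm. The trigger email may only start a process that the independent person completes, and a division of roles within the team is detail that a condensed article may leave to the full protocol. This stands in part: the principal researcher's knowledge is an inference. It does not dispose of the point, because the article makes a positive claim about researchers as a group and names the research team as sender of the links.

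The second reply is that the exception is disclosed and the rules are fixed. The disclosure is real but does not reach routine link-sending. The fixed rules do stand as a reason to expect little bias.

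A reader might infer more than the text supports:

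- **Master file.** Data Management and Monitoring describes a file that "matches the unique participant code to their self-generated code to ensure participants are allocated to the correct experimental group", which could suggest that the team holds the arm list. The file is said only to match two codes, and the same paragraph says the participant code does not reveal the group.
- **Task data.** Files are saved to the researcher's Inquisit account, but nothing says that they show the arm or that anyone opens them during the trial.
- **Exclusions.** The careless-responder rule is fixed, since all instructional items must be wrong, and leaves little room for judgment.
- **Model choice.** Nothing says that selection by AIC is made with arms visible. Masking of the analyst is commonly settled in a statistical analysis plan, which is not shown.

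None of these forms part of the point.

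**Conclusion.** The described procedure does not deliver researcher blinding throughout, and the technical-support exception does not close the gap. The conclusion rests on reading the Procedure section as written: the research team sends the links, and the links differ by arm. It would fall if a masked link scheme or a separate unblinded role existed, but the article describes neither.

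The consequence is confined mainly to attrition and sessions completed. The likely bias is modest, because reminder and dropout rules are largely fixed, and its size cannot be derived from the documents. The illustrative rejection rates depend wholly on an assumed shift and SD and should not be read as an estimate. Participant masking is a separate matter: Ethics and Dissemination says participants are not told of the three conditions, and this point does not dispute it. The matter should be corrected, but it does not invalidate the trial.

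**What to change.** In the randomization and procedure sections:

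- Allocate and release arm-specific links through an automatic redirect from survey to task. Alternatively, use one named unblinded person who has no participant contact and no part in the analysis. If that is the independent person who holds the list, amend the statement that this person is blinded to the intervention's processes, since releasing links would end that.
- Send the baseline-completion notice to that system or person.
- Issue invitations and reminders from one automatic template and timetable in all arms.
- Log each case in which technical support reveals an arm.
- Restate the blinding claim as what is delivered: participants are unaware of the three conditions, and team members are masked except for the link-release role and logged support cases.

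Recruitment began in August 2021 and was ongoing when the article was written. If the team has already sent links, report researchers as not fully blinded and interpret the engagement results accordingly.

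The cost is rerouting one email and the link release, setting up a message template and keeping a short log. No participants, visits or assessments are added.
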